### Randomization

Consenting women will be randomly allocated using block randomisation into one of three groups: control vs. smaller incentive ($AUS20) vs. larger incentive ($AUS40). The unit of randomisation will be the day and session time (i.e. morning or afternoon) of the patient’s first antenatal visit to minimise potential contamination and deception. Randomisation will be performed offsite, by an independent statistician prior to study initiation. Allocation of days of the week to groups will be done using Proc Plan in SAS.

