### Participants

A sample of ninety (90) consenting pregnant women will be recruited to participate. Women will be considered eligible if they are: (1) aged at least 16 years; (2) presenting for their first antenatal visit; (3) less than 31 weeks gestation; (4) sufficient in English language to complete the survey; and (5) a current smoker (defined as having smoked in last 7 days and a return a positive saliva sample for cotinine). Pregnant women will be ineligible to participate if they have elected to receive shared antenatal care with their GP and/or are considered by clinic staff to have a severe cognitive or psychiatric disorder; currently being treated for chemical dependency other than alcohol or tobacco; or have quit smoking before their first antenatal appointment.

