### Procedures

All women who visit the hospital antennal clinic will undergo their usual antenatal interview by the clinic nurse. During this interview patients are asked about their smoking status and basic demographic characteristics. At this time potentially eligible patients will be identified and informed that the study is being conducted within the clinic. If women are interested they will be directed to a Research Assistant (RA) who will be stationed within the clinic. The RA will provide interested women with information describing the study. If patients would like to take part in the study the RA will obtain their written informed consent. Women will then be asked to provide a saliva sample to confirm their smoking status and complete a 15-minute baseline Touchscreen computer survey, which will also ask for their on-screen consent.

If a woman’s initial antenatal appointment has been randomised to one of the two intervention groups, the RA will verbally explain the details of their incentive scheme, including, the schedule for monitoring, contingencies being offered and the rules of payment. All participants will be provided with a study package to take home with them, which will contain information about the study, referrals to Quit smoking self-help documents and a Quit telephone help number (provided by clinic midwives) and a letter of support to pass onto their partner. Consenting women will be asked to attend 8 intervention sessions, at which participants in the two intervention groups will be eligible to receive a reward. The 8 intervention sessions will occur approximately fortnightly, during participants’ scheduled antenatal appointments.

During each of the 8 intervention sessions, all women will be asked to indicate their current smoking status and whether they have quit smoking in the last 7 days. Women will also be asked to provide a saliva sample which will be analysed to confirm their self-report smoking abstinence. Those women in the intervention groups who self-report non-smoking and return a negative cotinine reading (level 0) will be provided with their monetary incentive. A similar follow-up procedure will occur seven more times (i.e. a total of 8 intervention sessions) during women’s scheduled antenatal appointment.

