### Primary outcomes

Proportions and frequencies will be calculated to assess the following outcomes: (i) participant consent rates; (ii) loss to follow-up rates; and (iii) participant compliance with saliva and hair cotinine analysis. Proportions and frequencies will also be calculated for all closed-ended questions included in the study participant and clinic staff interviews to allow investigation of: (iv) participant acceptability of touchscreen computers for self-reported smoking rates and demographics; and (v) acceptability of incentives to staff and study participants. Differences between experimental groups in the proportion of each of these five primary outcomes and the secondary outcome (proportion quit smoking) will be assessed through Fisher’s exact test. Differences between participant subgroups and these outcomes will also be assessed using Fisher’s exact test. Although p-values from the above will be reported, the focus will be on providing 95% confidence intervals around point estimates for comparisons of all three treatment arms.

Qualitative analysis will be performed on open-ended questions included in participant and staff interviews investigating the following primary outcomes: (vi) acceptability of saliva and hair cotinine analyses for biochemical validation of smoking status; and (vii) perceived barriers and facilitators to using financial incentives. All interviews will be transcribed verbatim and a thematic analysis will be performed independently by two of the research team members.

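### Session-level allocation fixed in advance leaves the arm known for later women in a session, and the between-arm test of consent cannot show an effect of incentive size

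*Protocol article*

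**What the plan says.** The Randomization section of the protocol article describes what is allocated in three ways. It first says "Consenting women will be randomly allocated using block randomisation into one of three groups". It then says "The unit of randomisation will be the day and session time (i.e. morning or afternoon) of the patient’s first antenatal visit", giving the reduction of contamination and deception as the reason. It ends with "Allocation of days of the week to groups will be done using Proc Plan in SAS". On timing and source it says "Randomisation will be performed offsite, by an independent statistician prior to study initiation".

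Under Procedures, the clinic nurse conducts the usual antenatal interview, and "At this time potentially eligible patients will be identified and informed that the study is being conducted within the clinic". Interested women go to the RA stationed in the clinic, who informs them and takes written consent. Saliva and the baseline survey follow. The next paragraph then says "If a woman’s initial antenatal appointment has been randomised to one of the two intervention groups, the RA will verbally explain the details" of the scheme.

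Consent is the first-listed primary outcome. The analysis of primary outcomes plans Fisher's exact test for "Differences between experimental groups in the proportion of each of these five primary outcomes", consent included, with the emphasis on 95% confidence intervals. The Sample size section also lists consent among the outcomes for which a difference between groups will be estimated.

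The Participants section includes women who smoked in the last 7 days and have a positive saliva test. It excludes those judged by clinic staff to have a severe cognitive or psychiatric disorder, and those who "or have quit smoking before their first antenatal appointment".

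**The concern.** Off-site generation by an independent statistician protects how the sequence is made. It does not hide the arm if the arm belongs to a calendar session and the person recruiting in that session also delivers its incentive explanation. Several entry steps leave room for judgement: which women are told about the study, who counts as interested, and the staff opinion on severe disorder. If these judgements are made with the arm known, the arms may differ in motivation to quit. The quit-rate comparison, meant to demonstrate potential effectiveness, would then carry a selection effect.

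The consent comparison raises a separate problem. A reader who sees different consent rates in the control, $20 and $40 arms will naturally take the difference as evidence of how attractive the incentive is. The order of steps under Procedures does not allow that reading.

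**Working it through.** **1. When the arm is fixed and who learns it.** Randomization: the session's arm is set before the study starts. Procedures: one RA informs, consents, takes the saliva that confirms eligibility, and explains the scheme where the session is an incentive session. Suppose the arm is hidden from the RA when the session opens. It becomes known once the first enrolled woman reaches the explanation step, and every later woman in that session is then approached with the arm known. If the allocation of weekdays is a repeating pattern, the arm of every slot is known after one cycle. The article does not say whether it repeats.

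**2. How many women are affected.** Inputs from the article: about 4,300 deliveries a year (Setting); 17% self-reported smokers, 10% ineligible, 60% consent (Sample size). As a check on these inputs, the number to approach is 90/(0.80 × 0.60 × 0.90) = 208.3, which reproduces the stated 208.

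Assumptions: 10 half-day sessions a week (the article gives only a 5-day service), and either all or half of the deliveries have a first visit at this clinic.

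- Smokers: 4,300 × 0.17 = 731 a year; 731/52 = 14.1 a week; 14.1/10 = 1.41 per session.
- Enrolments per session: λ = 1.41 × 0.90 × 0.60 = 0.76; at half volume, 0.38.
- Share of enrolments that are first in their session, if arrivals are Poisson: (1 − e^(−λ))/λ. At 0.76 this is 0.532/0.76 = 70%; at 0.38 it is 0.316/0.38 = 83%.
- Later in their session, so recruited with the arm known: 30% and 17%.
- Share of enrolled women with at least one other participant in the same first session: 1 − e^(−λ) = 53% and 32%. This matters for the alternative of individual allocation.

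**3. What the consent test can measure.** There are two cases.

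- The woman consents before hearing the scheme, as the written order has it. Incentive size cannot then affect her consent. A difference between arms is chance, a different mix of women by session, or recruiter behaviour. With 208 × 0.9/3 ≈ 62 eligible women per arm and 60% consent in both, Fisher's test at 5% is significant 3.5% of the time, by chance alone.
- The arm becomes known to her earlier. The appeal of the incentive and the recruiter's selection then cannot be separated.

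**4. Scale of a recruiter effect (assumed numbers).** With 62 eligible women in an arm and 60% consent, 37.2 consent. If staff do not approach 5, 10 or 15 women who would have refused, observed consent in that arm becomes 37.2/57 = 65.3%, 37.2/52 = 71.5% or 37.2/47 = 79.1%, with no true difference. For the middle case, the 95% half-width of the difference from 60% is 1.96 × √(0.60 × 0.40/62 + 0.715 × 0.285/52) = 17 points. A shift of 11.5 points would not stand out from sampling error.

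**The case against.** The strongest reply is that this is a condensed article. How the list is held and released is commonly left to the full protocol, and the RA strictly needs the arm only after consent, saliva and survey. That stands for the first woman in a session: a reader might infer that the nurse and RA know the arm from the start, but the article does not say so. It does not answer the case of later women, because their exposure follows from the session unit and the RA's stated role, not from an omitted detail.

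The reply also disposes of some stronger readings. A reader might infer that motivated women could be steered into paid sessions. The arm belongs to an appointment already under way when staff meet the woman, so they could only refer or enrol selectively. The positive saliva test limits discretion further. A reader might also see a contradiction between the 7-day inclusion rule and the exclusion of women who have already quit. Inclusion and exclusion criteria apply together, so what is wrong is that *quit* is undefined.

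On consent, the article stresses estimates over p-values and nowhere states that consent by arm will show the effect of incentive size. That is fair. The between-arm comparison is planned all the same, and no meaning about the incentive can be attached to it.

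Finally, session allocation has a stated purpose, contamination control, and quitting is a secondary outcome in a proof-of-concept trial declared underpowered for small differences. Both points bear on the severity and on the choice of remedy.

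**Conclusion.** The point holds as a should-fix. The design leaves the arm known for every woman after the first enrolled in a session, and earlier if weekdays repeat, so it is open to selective referral or enrolment by arm. The later-in-session share is about 17% to 30% of enrolments, which rests on 10 sessions a week, 0.38 to 0.76 enrolments per session and Poisson arrivals.

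The documents do not show that bias occurred, and they give no basis for a specific bias in quit rates; any such figure would rest on assumed quit rates and motivation.

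The between-arm test of consent cannot inform feasibility by incentive size. A reader might infer that the consent outcome as a whole is lost, but the pooled rate remains valid.

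**What to change.** - **Randomization:** keep the session as the unit and reconcile the three descriptions of what is allocated. Allocate calendar-dated sessions, not fixed weekdays, in blocks of varying size. Prepare one sealed allocation per session.
- **Procedures:** open it only after the first woman's consent, saliva result and baseline survey are recorded. Keep the referring nurses unaware of it.
- **Sample size and Analysis (primary outcomes):** report one overall consent rate with its 95% confidence interval. Show consent by arm only as a check on concealment.
- **Participants:** clarify how the exclusion for having quit before the first appointment relates to having smoked in the last 7 days.

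The cost is protocol wording and sealed envelopes, with no extra participants. The remaining weakness is that later women in a session, roughly 17% to 30% of enrolments on the assumptions above, stay unconcealed. Individual allocation after the baseline survey would conceal every woman. However, about 32% to 53% of enrolled women would share a first session with another participant, possibly in a different arm, so it trades away the contamination control that the article gives as its reason for session allocation.

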### Setting

The study will take place at the antenatal clinic within a large public teaching hospital in New South Wales, Australia. The antenatal clinic operates a 5 days-a-week service with most women presenting for an average of 6 to 8 clinic visits over the course of their pregnancy. The hospital manages approximately 4,300 deliveries each year with the majority of these women receiving antenatal care predominantly through the hospital antenatal clinic.

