### Sample size

A convenience sample size totalling 90 women will be recruited, with 30 women randomised to each of the three study groups. As this is a proof-of-concept trial, the sample size will not be adequately powered to detected small differences however a sample size of 30 women in each group will allow for detection of a difference in smoking rates between groups of 24%, with 5% significance level and 68% power. Based on previous studies, this will be sufficient to provide an estimate of the difference in proportions between groups for the following primary outcomes: (i) consent rates; (ii) lost to follow-up rates; (iii) participant compliance to saliva and hair cotinine analysis; (iv) acceptability of incentives and validation measures, and the secondary outcome variable, smoking cessation. To allow for a 20% drop-out rate, a consent rate of 60% and 10% of women being ineligible, 208 pregnant women who smoke will be approached. Based on a previous study conducted by the investigators, approximately 17% of women seen at this clinic are self-reported smokers
[21].

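### Clinic sessions are randomised, but the sample size and the tests treat women as the unit, and the text does not settle whether weekday slots are fixed to arms

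*Protocol article*

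**What the plan says.** All references are to the protocol article.

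- **Randomization** opens with women as the unit: "Consenting women will be randomly allocated using block randomisation into one of three groups". It then gives a different unit: "The unit of randomisation will be the day and session time (i.e. morning or afternoon") of the first antenatal visit, chosen to limit contamination and deception. It ends: "Allocation of days of the week to groups will be done using Proc Plan in SAS". The list is made offsite by an independent statistician before the study starts.
- **Procedures** agrees with the session as unit. The incentive scheme is explained to a woman if her "initial antenatal appointment has been randomised to one of the two intervention groups".
- **Setting**: "The antenatal clinic operates a 5 days-a-week service".
- **Sample size** returns to women: "A convenience sample size totalling 90 women will be recruited, with 30 women randomised to each of the three study groups". The Method paragraph of the Abstract says the same. Power is quoted at 68% for a difference of 24 percentage points, with no number of sessions, cluster size, intracluster correlation or design effect.
- **Primary outcomes** (under Analysis): "Differences between experimental groups in the proportion of each of these five primary outcomes", and in the proportion who quit, are tested by Fisher's exact test, with the stated focus on 95% confidence intervals between arms. The Quit rates subsection uses Fisher's test again, and Kruskal-Wallis for the PHQ2. None of these has a session or weekday term.

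**The concern.** If a session carries the arm, every woman whose first visit falls in it gets the same arm, and the trial is cluster randomised. Fisher's test and ordinary intervals for a difference in proportions assume that women are independent. Where women in the same slot resemble each other more than women in different slots, those intervals are too narrow. The intervals are what the protocol says it will rely on.

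The last sentence of the Randomization section raises a second issue. If weekdays, or weekday half-days, are assigned to arms once, an arm consists of a handful of slots. Differences between slots in staff or case mix then sit inside the comparison between arms, and no analysis can take them out after recruitment.

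**Working it through.** **1. Which unit applies.** The first sentence of the Randomization section has women allocated after consent. The unit sentence, and the Procedures section, have the appointment carrying the arm. The Primary outcomes section compares consent rates between arms, which is possible only if women who decline already have an arm. So allocation precedes consent and the session is the operative unit. The wording about randomised women is what conflicts.

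**2. The plan's own figures.** The number approached reproduces: 90 / (0.8 × 0.6 × 0.9) = 208.3, stated as 208, with no factor for clustering. The 68% power cannot be pinned down, because no control rate is given. It is consistent with 30 independent women per arm: a two-sided pooled test gives 68.6% at 6% v 30% and 66.6% at 7% v 31%.

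**3. Reading A: slots fixed to arms.**
- Half-day slots: 5 × 2 = 10, split 3/3/4. Whole days: 5, split 2/2/1. Neither divides by three. With equal recruitment per slot and no cap, 90 women fall about 27/27/36 or 36/36/18.
- With three slots against three there are C(6,3) = 20 possible allocations, so the smallest two-sided randomisation p-value is 2/20 = 0.10.
- Design effect = 1 + (m − 1) × ICC. The ICC (intracluster correlation) is not in the document; 0.01 to 0.10 is an assumption. With 10 slots, m = 90/10 = 9. Intervals should be wider by the square root of the design effect. Power is for 6% v 30%, starting from 68.6%:

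| ICC | Design effect | Interval should be wider by | Power |
|---|---|---|---|
| 0.01 | 1.08 | 4% | 65% |
| 0.02 | 1.16 | 8% | 62% |
| 0.05 | 1.40 | 18% | 54% |
| 0.10 | 1.80 | 34% | 44% |

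- Simulation with no true difference (beta-binomial, 3 slots of 10 women per arm, outcome 20%, Newcombe interval, Fisher's test at 5%). Ranges span repeated runs:

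| ICC | Coverage of the nominal 95% interval | Fisher rejection rate |
|---|---|---|
| 0 | 95.2–95.5% | 2.2–2.5% |
| 0.02 | 93.4–93.5% | 3.4–3.5% |
| 0.05 | 90.3–90.4% | 5.7–5.9% |
| 0.10 | 85.3–85.6% | 9.6–9.7% |

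- With a 10% outcome and ICC 0.05, coverage is about 93.6% and Fisher's rejection rate about 3%.

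**4. Reading B: each calendar half-day randomised.** Inputs: 4,300 deliveries a year (Setting), 17% smokers, 10% ineligible and 60% consent (Sample size). Assumptions: every delivery attends the clinic, and there are 10 × 52 = 520 half-days a year.
- Consenting women per session = 4,300 × 0.17 × 0.9 × 0.6 / 520 = 0.76.
- For Poisson counts the size-weighted cluster size is 1 + 0.76 = 1.76. At ICC 0.10 the design effect is 1 + 0.76 × 0.10 = 1.08 and intervals should be 4% wider. At ICC 0.01 the figures are 1.01 and 0.4%.
- Simulation with 30 women per arm and a 20% outcome: coverage about 95% and Fisher rejection 2.4–2.7% at ICC 0.05 and 0.10.

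**The case against.** The strongest reply is that the harm belongs to one reading only. Block randomisation, and an appointment that is itself randomised, fit a rotating list of calendar sessions at least as well as a one-off assignment of weekdays. Under that reading the intervals are sound. Even with fixed slots, real damage needs an ICC of about 0.05 or more between half-days of one clinic; Fisher's test is conservative and stays below 5% at 0.02. The trial is also a pilot with a convenience sample, admits low power, and puts feasibility first. All of this stands. It limits the size of the point but not the inconsistency, because the article itself names the unit, the test and the power basis.

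Three stronger readings are tempting, and the documents do not support them.
- **That the intervals are too narrow as a matter of fact.** This holds only with fixed slots and a positive ICC that matters; the document establishes neither.
- **That arm equals weekday.** With half-day slots, Monday morning and Monday afternoon can be in different arms. Arm is then tied to a few slots. Full weekday confounding needs whole-day allocation, which does not fit the morning or afternoon wording.
- **That staff know the arm before inviting a woman.** The article does not say who holds the list. It places consent, saliva sample and baseline survey before the scheme is explained, and a condensed article may leave concealment to the full protocol. A fixed weekday list would be predictable, but selective recruitment is a possibility and not a finding.

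**Conclusion.** The stated analysis does not match the stated unit of randomisation, and the Randomization section contradicts itself on what is randomised. That part is certain.

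The consequence is conditional. With slots fixed to arms, each arm rests on one to four slots, slot effects cannot be separated from the incentive effect, and women-level intervals under-cover, from slightly at ICC 0.02 to seriously at 0.10. With calendar sessions randomised, the design effect is near 1 and the intervals are essentially correct. The ICC values, the 20% outcome, equal recruitment across slots and the attendance figures are assumptions.

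This should be fixed. It becomes a must-fix if weekday slots are in fact fixed, because that confounding cannot be undone once recruitment is over.

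**What to change.** 1. **Randomization.** State one unit. Allocate calendar half-day sessions in permuted blocks within each weekday × morning/afternoon slot, so that every slot rotates through all three arms. At 0.76 women per session, 90 women need about 90 / 0.76 = 118 sessions, or about 12 occurrences of each of the 10 slots, so rotation is practicable. Where feasible, do not disclose a session's arm to recruiting staff until consent and baseline are complete. Remove or reword the sentences about allocating consenting women and days of the week.
2. **Primary outcomes and Quit rates.** Base between-arm tests and 95% intervals on the session, by re-randomisation within blocks or with cluster-robust intervals. Say that the change is expected to be small under calendar sessions.
3. **Abstract and Sample size.** Say that sessions are randomised with about 30 women expected per arm, and that the 68% power assumes independent women.

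Cost: a new allocation list and revised wording, slightly wider intervals, and arm sizes that will not be exactly 30. No extra patients or procedures.
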